### Additional Endpoints:

1. Reduction of IOH duration at MAP  $\leq$  60 mmHg;
2. Area under threshold MAP < 65 mmHg
3. Acute kidney injury (AKIN criteria);
4. Quality of recovery (QoR-15) on postoperative day 3;
5. Postoperative morbidity survey (POMS) on postoperative day 3;
6. Amount of red blood cells infused (ml packed red blood cells);
7. Amount of intraoperative fluid (crystalloid and colloid);
8. Amount of vasoactive medications (i.e. phenylephrine, ephedrine, nor-epinephrine, (1)epinephrine, dobutamine);
9. Advanced hemodynamic variables at 20-sec intervals:
  - a. Hypotension prediction index (HPI)
  - b. Cardiac output (CO);
  - c. Cardiac Index (CI);
  - d. Stroke Volume (SV)
  - e. Stroke Volume Index (SVI);
  - f. Stroke Volume Variation (SVV);
  - g. Dynamic arterial elastance (Edyn);
  - h. Maximal slope of the arterial pressure upstroke (dP/dt);
  - i. MAP & PR
10. Hospital length of stay;
11. ICU Hospital length of stay
12. Hospital readmission within 30 days;
13. Cardiovascular mortality at 30 days;

14. Composite of systemic inflammatory response syndrome (SIRS) and at least one major organ dysfunction for renal, cardiovascular, respiratory, neurologic and coagulation systems by day 7 after surgery (2);
15. Acute respiratory distress syndrome (3);
16. Acute pulmonary edema (3);
17. Superficial or deep surgical site infection (3);
18. Hospital acquired infection (4);
19. Ventilator time.

**Patient Population:** Subjects recruited and enrolled should be classified as American Society of Anesthesiologist (ASA) physical status 3-4 who are scheduled for moderate-to-high-risk non-cardiac surgery and will be receiving pressure monitoring with an arterial line. Potentially qualifying patients will be evaluated during their preoperative anesthesia clinic visits. ...

**Study Design:** A prospective, single-arm, open-label, multicenter post-approval study to determine whether the use of the Acumen™ HPI Feature Software to guide intraoperative hemodynamic management in non-cardiac surgery reduces the duration of intraoperative hypotension below a threshold of Mean Arterial Pressure (MAP).

**Number of Patients:** Up to 485 eligible subjects at up to 20 US study sites. The control group is comprised of 19446 patients. This number of controls is fixed and will not be altered.

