### II. Study Design

This study is a prospective single-arm open-label multi-center post-approval study to determine whether the use of the Acumen™ HPI Feature Software to guide intraoperative hemodynamic management in non-cardiac surgery reduces the duration of intraoperative hypotension below a threshold of Mean Arterial Pressure (MAP). The comparison group for this study is a retrospective historical control group with patient-level data from the Multicenter Perioperative Outcomes Group (MPOG). The intention is to conduct the active therapeutic study at clinical centers enrolled in MPOG with HPI study patients being selected from the same centers. The methods described below are intended to provide a comprehensive analysis of the safety and effectiveness of the study data.

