### **1. Sample Size Computation**

Recent analysis from the Multicenter Perioperative Outcome Group (MPOG) evaluated the mean duration of IOH in a subset of participating sites, during calendar year 2017, who met the eligibility criteria of this HPI Study. The analysis resulted in a total of 19446 patients with at least one minute of IOH and demonstrated a mean duration of IOH of 28.2 minutes with standard deviation 42.5.

It is anticipated that the HPI system will reduce that number of minutes by about 25%. Because the size of the standard deviation (SD) of the minutes in IOH decreases with decreasing mean. Estimates from other literature suggest that the SD is a similar fraction of the mean within the range. For this computation we assume that the ratio of the standard deviation to the mean remains constant. The ratio of the standard deviation of the mean from these data is  $42.5/28.2 = 1.50$ . To protect against the uncertainty of the ratio under powering the study, additional computations were done to make the estimate more conservative with a SD to mean ratio of 1.65. The minimum recommended required sample size, using Pass 14, of 389 completed subjects for 90% power for a one-sided  $\alpha = 0.025$  test which were derived from the additional computations of standard deviation ratios. Assuming an attrition for a less than 3-hour surgery of 10% and a small loss to follow-up of 4%, the recruited sample size should be  $389/0.86 \approx 452$  for 90% power in the Pivotal cohort. Therefore, the sample size for this study will be capped at 485, including up to 33 roll-in subjects and up to 452 Pivotal subjects, for a minimum of 90% power. Roll-in subjects will be analyzed separately from Pivotal subjects.

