## D. Primary Effectiveness

Recall that the study subjects were drawn from the same study sites that were used for the MPOG estimates from the control population. Because the sites may represent different patient populations, it is likely that the estimates from the site may be heterogeneous as were the estimates for the control MPOG sample. In an ideal world the proportion of subjects in the study will be similar to that from the MPOG controls, but the dynamics of study conduct usually result in a different subject distribution depending on which study sites were entered into the study earlier rather than later. In order to provide an estimate from the study sample that is most comparable to the controls adjusting for site the primary effectiveness endpoint will be done with a weighted average of site means and standard deviations as described below.

The study subjects will have the mean and standard deviation of the durations of IOH during the study computed by study site. To generate an estimate across the range of estimates for comparison to the MPOG controls, the estimates from each study site will be weighted and combined in the same proportion of subjects that were included in the control sample from MPOG. This method is analogous to direct standardization used in epidemiology (Fleiss et al (2003)). This weighted average and its properly computed standard deviation will be compared to the estimates obtained from MPOG by a one-sided unequal variance two-sample t-test. If this test is statistically significant with  $P<0.025$ , the primary effectiveness endpoint will be a success. If the proportion of subjects in the

control sample is  $p_k$  for study site  $k$  and the estimate of the mean from study site  $k$  is  $\bar{x}_k$ , then the study estimate from the interim sample for the overall mean is given below.

$$\bar{x} = \sum_k p_k \bar{x}_k.$$

If the standard deviation for study site  $k$  is  $s_k$ , then the estimate of the interim standard deviation is given below.

$$s = \sqrt{\sum_k (p_k s_k)^2}.$$

The test statistic for the interim is taken from the formula below.

$$t = \frac{\bar{x} - \bar{x}_{MPOG}}{\sqrt{\frac{s^2}{n} + \frac{s_{MPOG}^2}{n_{MPOG}}}}.$$

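### The primary site-weighted mean has no rule for control sites without an analysed HPI subject, so the weights may not sum to 1 and the comparator may cover sites that the treated mean does not

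*SAP*

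**What the plan says.** SAP IX.D (Primary Effectiveness) computes a mean and SD of hypotension duration at each study site. These "will be weighted and combined in the same proportion of subjects that were included in the control sample from MPOG". With p_k the control-sample proportion for site k, the treated estimate is x̄ = Σ p_k x̄_k. It is compared with x̄_MPOG in a one-sided unequal-variance t-test at 0.025, whose control term is s²_MPOG / n_MPOG. The text labels these formulas as interim although section VIII plans no interim analysis. They are read here as the final ones, since no others are given.

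The Analysis Summary (Number of Patients) states: "The control group is comprised of 19446 patients. This number of controls is fixed and will not be altered". V.A.1 (Sample Size Computation) says the controls were found "in a subset of participating sites, during calendar year 2017", and that this sample "demonstrated a mean duration of IOH of 28.2 minutes with standard deviation 42.5".

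On site overlap, II (Study Design) says: "The intention is to conduct the active therapeutic study at clinical centers enrolled in MPOG". IX.D goes further and states as fact that the HPI subjects came from the sites behind the control estimates. It also expects site estimates to be heterogeneous and the spread of subjects over sites to differ from that of the controls. No section says what happens when a control site has no analysed HPI subject.

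**The concern.** Direct standardisation works when the weights sum to 1 and both sides of the comparison cover the same strata. The written rule secures neither. That HPI subjects come from control sites places the study sites among the control sites. It does not say that every control site contributes, which is the condition needed.

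The condition could fail in ordinary conduct. The number of control sites is not given, and the cap of 20 study sites is not tied to it. The test uses the FAS, which requires surgery of at least 3 hours and a postoperative assessment (IV.B), and roll-in subjects are analysed separately (V.A.1). A small site could therefore enrol and still supply nobody to the test.

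This is the trial's only confirmatory test. Durations cannot be negative, so under the literal formula each missing term p_k x̄_k can only lower the treated mean, which is the direction of success. The sensitivity analysis that ignores surgery duration (end of IX.D) reuses the same weighting, so it would not reliably expose the problem.

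**Working it through.** **Inputs.** From V.A.1: control mean 28.2 min, SD 42.5, n_MPOG = 19446; planned reduction 25%, so δ = 0.25 × 28.2 = 7.05 min; 389 completed subjects; 90% power; one-sided α = 0.025. Assumed, because the SAP does not give it: w, the share of controls at sites with no analysed HPI subject.

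**The plan's own figure.** With SD 42.5 in both groups and the control n fixed:

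n_T = 42.5² / [(7.05 / (1.960 + 1.282))² − 42.5²/19446] = 1806.25 / (4.730 − 0.093) ≈ 389.5

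Power at 389 is 0.900, so the stated 389 is reproduced, and SD 42.5 is used below. (The stated SD-to-mean ratio of 1.65, applied to the treated mean, gives 263 to 264 instead. That is a separate matter.)

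**Literal formula, no device effect, equal site means.** The weights sum to 1 − w, so E(x̄) = (1 − w) × 28.2. With an otherwise correct standard error,

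P(success) = Φ( w × 28.2 / √[(1 − w)² × 42.5²/389 + 42.5²/19446] − 1.96 )

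where 42.5²/389 = 4.643 and 42.5²/19446 = 0.093.

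| w | treated mean (min) | spurious reduction (min) | SE | false success |
|---|---|---|---|---|
| 0 | 28.20 | 0 | 2.18 | 0.025 |
| 2.5% | 27.49 | 0.71 | 2.12 | 0.052 |
| 5% | 26.79 | 1.41 | 2.07 | 0.101 |
| 10% | 25.38 | 2.82 | 1.96 | 0.300 |

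With SD 46.53 (1.65 × 28.2) the last two rows become 0.091 and 0.259. The table takes the standard error as correct in order to isolate the weighting. The SAP's own formula for s, followed by s²/n, is a different question and is not counted here.

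**Rescaled weights, equal site means.** Dividing by Σ p_k returns the treated mean to 28.2 for every w, and false success to 0.025.

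**Rescaled weights, unequal site means.** Let the unrepresented sites differ from the others by d minutes on average. The all-control mean then differs from the mean of the represented sites by w × d. As an illustration with assumed figures, take w = 20% and SE 2.18:
- d = +10: spurious reduction 0.20 × 10 = 2.0 min; false success Φ(2.0/2.18 − 1.96) ≈ 0.15.
- d = −10: the shift is 2.0 min the other way; false success Φ(−2.0/2.18 − 1.96) ≈ 0.002. Power for a true 7.05 min reduction falls from 0.90 to Φ((7.05 − 2.0)/2.18 − 1.96) ≈ 0.64.

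This part of the bias can therefore favour or penalise the device.

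**The case against.** The strongest answer is that IX.D calls its estimate a weighted average and likens it to direct standardisation. Both imply weights that sum to 1, and p_k is introduced per study site, so it can be read as the control share among study sites. A competent programmer would probably rescale. This stands: the formula is under-specified, and the plan does not actually prescribe unnormalised weights. It does not settle the matter, because rescaling still leaves a comparator that includes unrepresented sites.

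A reader might infer that site matching is no more than an intention. II uses that word, but IX.D states the overlap as fact. On the SAP's own terms, a study site without controls should not occur.

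A reader might also infer that IX.D predicts empty sites. It predicts unequal enrolment depending on when sites entered, which the weighting is designed to handle. An empty site is possible but is not forecast.

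A further point is that freezing the controls at 19446 is a safeguard, since it fixes the external comparator in advance. That also stands, and the remedy should keep the dataset frozen.

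Finally, VII plans a site sensitivity analysis, and IX.D a mixed model if patient-level control data can be obtained. These would examine site effects, but they are supportive and do not change the success decision.

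**Conclusion.** The gap is real but conditional, and it should be fixed. If every control site supplies analysed subjects, the weights sum to 1 and the problem vanishes. If not, the literal formula biases the treated mean downwards by about w × 28.2 min, and a share of only 2.5% roughly doubles the nominal 0.025 error. With rescaled weights, what remains is a site-mix bias of w × d, of unknown sign.

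The false-success figures assume no effect, equal site means, n = 389, SD 42.5 and a correct standard error. They apply only to the unnormalised reading. A reader might take larger values of w as evidence that the test is bound to succeed: at w = 25% the artefact is 7.05 min and false success is 0.99. The SAP does not support that inference. It gives no per-site control counts, and the 25% case matches the planned effect only because w was set to the same percentage.

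**What to change.** In IX.D, define p_k = N_k / Σ N_k, where N_k is the number of controls at site k and the sum runs over sites with both MPOG controls and at least 2 FAS subjects (two are needed to compute s_k). The weights then sum to 1. Compute x̄_MPOG, s_MPOG and n_MPOG from those same sites for the primary test.

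Keep the 2017 control dataset frozen. Amend the Number of Patients entry to say that the dataset is fixed, while the primary comparison uses its site-matched subset under this pre-specified rule. Report the comparison with all 19446 controls as a sensitivity analysis, and report subjects from any site without controls separately.

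The cost is SAP wording and a table of control mean, SD and n by site. The control n may fall, the benchmark may move from 28.2 min, and the subset used will depend on which sites enrol, so the rule must be fixed before outcomes are seen. The loss of precision is negligible. Control variance is 0.093 of a total of 4.643 + 0.093 = 4.74, about 2%. Halving the controls would raise it only to 0.19, and the standard error from 2.18 to √(4.643 + 0.186) = 2.20.

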## **VI. Multiplicity**

The testing for the primary effectiveness analysis will be a one-sided 0.025 test. The primary effectiveness analysis must meet its objective of statistical significance. After analysis of the primary effectiveness endpoint, if the primary analysis results in statistical significance, the descriptive secondary effectiveness endpoints will be presented with nominal two-sided 95% confidence intervals. Thus, the study will be protected from alpha inflation by the closed form hierarchical method. Multivariate analyses are considered supportive without control of alpha and the additional endpoint analyses are likewise supportive without control of alpha.

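### The primary test divides the wrong variance by n: its standard error is too small whenever there is more than one site, and the nominal one-sided 2.5% error becomes about 18–30% with 5 to 20 equal sites

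*SAP*

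**What the plan says.** SAP section IX.D (Primary Effectiveness) computes the mean and SD of hypotension duration at each study site. The site results are then "weighted and combined in the same proportion of subjects that were included in the control sample from MPOG", which gives x̄ = Σp_k x̄_k, with p_k the share of the control sample at site k.

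The prose promises a sound measure of spread: "This weighted average and its properly computed standard deviation will be compared to the estimates obtained from MPOG", by a one-sided unequal-variance t-test. The formula that follows is introduced with "If the standard deviation for study site" k is s_k, and "then the estimate of the interim standard deviation is given below":

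- s = √Σ(p_k s_k)²

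Then "The test statistic for the interim is taken from the formula below":

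- t = (x̄ − x̄_MPOG) / √(s²/n + s²_MPOG/n_MPOG)

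Section VI (Multiplicity) fixes the error rate: "The testing for the primary effectiveness analysis will be a one-sided 0.025 test". Section VIII states that no interim analysis will be done. Despite their label, these are therefore the only formulas the SAP gives for the final primary test.

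**The concern.** The formula mixes two calculations. Squaring the weights is right when each term is the variance of a site mean, s_k²/n_k. Here each term is the variance of single patients, s_k², and the sum is then divided by the total n. The site sample sizes appear nowhere.

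A simple case shows the fault. Suppose enrolment matches the control mix exactly (p_k = n_k/n) and all sites share one mean and one SD, σ. The weighted mean is then the ordinary sample mean, with variance σ²/n. The printed formula gives σ²Σp_k²/n. Apparent precision grows merely because the same patients are divided among more sites, and the formula is right only for a single site.

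This test alone decides whether the study succeeds. If its standard error is too small, a modest chance difference from a historical control would be declared a proven benefit. The fault also carries into two sensitivity analyses in section IX.D that rest on the weighted site estimates: the ten imputed tests, and the analysis of all subjects whatever the length of surgery.

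**Working it through.** **Inputs from the SAP**

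- Controls: the SAP's MPOG analysis "demonstrated a mean duration of IOH of 28.2 minutes with standard deviation 42.5" (section V.A.1); "The control group is comprised of 19446 patients" (Analysis Summary, number of patients).
- Treated subjects analysed: n = 389; anticipated reduction about 25%, that is 0.25 × 28.2 = 7.05 min (section V.A.1).
- One-sided α = 0.025, z = 1.96; power 90%, z = 1.2816.
- Sites: up to 20. The actual number and the p_k are not given, so I take 2 to 20 equal sites as an assumed range.

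**Step 1. The SAP's own sample size**

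Use the ordinary two-sample variance, with SD 42.5 in both groups and controls fixed at 19446:

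n = 42.5² / [(7.05/(1.96 + 1.2816))² − 42.5²/19446] = 1806.25 / (4.730 − 0.093) ≈ 389.5

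This agrees with the stated 389, and 389/0.86 = 452.3 agrees with the stated 452. The sample size thus fits a treated-arm variance of σ²/n, not the printed formula. (A separate point: the stated SD-to-mean ratio of 1.65 at the treated mean of 21.15 gives SD 34.9 and n ≈ 263, not 389.)

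**Step 2. True and printed standard errors, no treatment effect, K equal sites**

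- Treated-arm term: 1806.25/389 = 4.643. Control term: 1806.25/19446 = 0.093.
- True SE = √(4.643 + 0.093) = 2.18 min, whatever K is.
- Printed SE = √(4.643/K + 0.093).
- Actual type I error = Φ(−1.96 × printed SE / true SE).
- Reduction needed for success = 1.96 × SE.

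| Equal sites K | Printed SE (min) | True SE / printed SE | Actual one-sided error | Reduction needed with printed SE |
|---|---|---|---|---|
| 2 | 1.55 | 1.40 | 8.1% | 3.0 min (11%) |
| 3 | 1.28 | 1.70 | 12.4% | 2.5 min (9%) |
| 5 | 1.01 | 2.15 | 18.1% | 2.0 min (7%) |
| 10 | 0.75 | 2.92 | 25.1% | 1.5 min (5%) |
| 20 | 0.57 | 3.82 | 30.4% | 1.1 min (4%) |

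With the correct SE the reduction needed is 1.96 × 2.18 ≈ 4.3 min (15% of 28.2).

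The treated-arm term is too small by exactly √K on the SE scale. For the whole SE the factor is a little less (2.15, 2.92 and 3.82 against √K of 2.24, 3.16 and 4.47), because the control term is unaffected.

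**Step 3. Simulation**

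With 8,000 runs and normal data, equal sites gave 17.4%, 25.4% and 30.0% for K = 5, 10 and 20. Over the unequal weights and enrolments tried with 5 to 20 sites, the range was 17–32%. Gamma data with the SAP's mean and SD gave 19–35% across all layouts. With the correct SE the same runs gave 2.1–2.7% for normal data and 3.6–6.0% for gamma data.

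**Step 4. Unequal weights**

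When enrolment follows the control mix and SDs are equal, the number that matters is 1/Σp_k², not the raw site count. As an illustration, take five sites with weights 0.6, 0.1, 0.1, 0.1 and 0.1:

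- Σp_k² = 0.36 + 0.04 = 0.40
- Printed SE = √(4.643 × 0.40 + 0.093) = 1.40
- Type I error = Φ(−1.96 × 1.40/2.18) = 10.4%

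**The case against.** The algebra cannot be defended. Reading s_k as a site standard error does not rescue it: s would then already be the SE of the weighted mean, and dividing by n again would make it worse. The serious objections concern size, intent and remedy.

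- **The size is conditional.** The SAP gives neither the number of sites nor the weights, and section IX.D itself expects an uneven distribution of subjects. Few sites, or one dominant site, give 8–12% rather than 18–30%. This stands, and the range should be quoted with its assumption. Every multi-site case still exceeds 2.5%.
- **The formulas may be a leftover.** They are called interim three times in a study without an interim. The prose promises a properly computed SD, and the sample size agrees with the ordinary variance. The final analysis might therefore have been programmed correctly. That is possible, but the SAP offers no other formula, and an analyst following it would use this one.
- **Correcting the SE does not guarantee exactly 2.5%.** The endpoint is strongly skewed (SD/mean 1.50), and the gamma simulations left 3.6–6.0%. This stands. It is a smaller, separate problem.
- **The correction may cost power.** The 90% holds only if enrolment roughly follows the control mix. As an illustration, take ten sites with assumed weights in the ratio 1:2:…:10. The correct SE is 2.18 with matching enrolment, 2.45 with equal enrolment and 4.01 with reversed enrolment. Power for 7.05 min, Φ(7.05/SE − 1.96), is then 90%, 82% and 42%. This stands too, but it is the real precision of the chosen estimator, which the printed formula conceals.

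**Conclusion.** The concern holds and must be fixed before analysis. The printed SE of the primary test is wrong for any study with more than one site, and nothing elsewhere in the SAP corrects it. At SD 42.5, 389 subjects, 19446 controls and no treatment effect, the one-sided type I error is about 18%, 25% and 30% for 5, 10 and 20 equal sites, and 8% and 12% for 2 and 3. These figures assume equal sites with a common SD; the exact value depends on the unknown weights and site enrolment. The direction does not: the test declares success too easily. With 5 to 20 equal sites a reduction of only 4–7% would count as success, against the 15% needed with the correct SE and the 25% anticipated.

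**What to change.** In section IX.D, replace the formulas for s and t with

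t = (Σp_k x̄_k − x̄_MPOG) / √(V_T + V_C), with V_T = Σp_k² s_k²/n_k and V_C = s²_MPOG/n_MPOG,

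and Satterthwaite degrees of freedom

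(V_T + V_C)² / [Σ(p_k² s_k²/n_k)²/(n_k − 1) + V_C²/(n_MPOG − 1)].

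In addition:

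- State in advance how a site with fewer than two analysed subjects is merged with another, so that every s_k exists. Name the merging rule, so that it cannot be chosen after the data are seen.
- Remove the three uses of interim, in line with section VIII.
- Use the same standard error in the imputed tests and in the analysis of all surgery durations.
- Because of the skewness, consider checking the corrected test with a site-stratified bootstrap, specified beforehand.

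The cost is a change of SAP wording and a small change of code. The planned 389 was already consistent with the ordinary variance, so no increase follows if site enrolment stays close to the control mix. If it does not, power will be below 90%, and the SAP should say so or enrolment by site should be watched.

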## C. Patient Accountability and Missing Data

A summary table will provide the total number of subjects enrolled and completed. The subjects eligible for and compliant with each follow-up contact will be summarized descriptively. Subjects withdrawn will be tabulated with their reasons for withdrawal.

Every effort will be made to collect all data points in the study. The sponsor plans to minimize the amount of missing data by appropriate management of the prospective clinical study, proper screening of study subjects, and training of participating investigators, monitors and study coordinators. The sponsor will provide a list of subjects who do not complete the trial along with the best information available on why they each left the trial prematurely.

While no imputation will be done for this study, sensitivity analysis by developing multivariate models of duration of IOH as a function of baseline and preoperative characteristics. If successful, the models may allow regression imputation for subjects with that are considered missing at random. Subjects with missing data that result from adverse events related to the test device or its use will be counted as not missing at random and will be imputed in the sensitivity analysis by random selection of a value with the same mean and SD as the untreated control distribution. Missing at random subjects will be imputed by random selection from a distribution with the same mean and SD as the treated subjects who have complete data.

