There are several sensitivity analyses to be done after the completion of the primary analysis. Assuming de-identified patient level data is available from MPOG, a multivariable mixed models analysis of variance will be done to determine if there are relevant impacts of patient characteristics that may impact the primary endpoint. Factors of concern will include gender, age, race, BMI, prior history of hypotension, prior history of heart disease, prior history of smoking, angiotensin receptor blockers, calcium channel blockers and ace inhibitors, ASA status, baseline MAP, history of coagulopathy, surgical time, intra-operative blood loss, diabetes, development of sepsis as an AE, chronic pulmonary disease and any baseline characteristic found out of balance by treatment group or study site. Factors will initially be screened with models that include treatment, the factor of interest, and the interaction between the two. Because of the increased power of the control sample, many of these comparisons could be statistically significant but not clinically significant. The screened factors will be evaluated to determine which should be included in a competition for the final model. This analysis will be done by backward elimination with no factors remaining in the final model with  $P > 0.05$ .

If it is not possible to get patient level data from MPOG, it may be possible for MPOG to perform the modeling by supplying them with the de-identified study data from our subjects.

From the model developed above, a second sensitivity analysis can be done to attempt to estimate the duration of IOH in subjects with missing data based on the model-based regression imputation (Little and Rubin, 2002). If a plausible model can be obtained, the imputation will be done with 10 different randomization seeds yielding ten populations from which a statistical test of the weighted site estimates can be used to provide supporting analysis to that done for the primary endpoint. The 10 imputed tests will be combined by the method of Rubin (1987) (this method is the substance of the SAS procedure MIANALYZE). The imputations will be done consistent with the guidance from the National Research Council Committee on National Statistics (2010).

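### The sensitivity model against the MPOG controls admits sepsis as an AE and intra-operative blood loss as covariates, which can bias the adjusted device effect, and the SAP describes the imputation model built on it in two ways

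*SAP*

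**What the plan says.** The primary comparison in SAP section IX.D is a site-weighted t-test against MPOG, with no patient-level covariates. The section then goes further: "There are several sensitivity analyses to be done after the completion of the primary analysis". The first of these is a multivariable mixed model, to be run if patient-level MPOG data are available or if MPOG can fit it using the study data. Its aim is "to determine if there are relevant impacts of patient characteristics that may impact the primary endpoint". Most candidate factors are preoperative: demographics, medical history, antihypertensive drugs, ASA class and baseline MAP. The same list also contains "surgical time, intra-operative blood loss, diabetes, development of sepsis as an AE".

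Selection runs in three steps. First, "Factors will initially be screened with models that include treatment, the factor of interest, and the interaction between the two". Second, the screened factors are reviewed for entry. Third, "This analysis will be done by backward elimination with no factors remaining in the final model" with P above 0.05.

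The model is then reused: "From the model developed above, a second sensitivity analysis can be done", which is regression imputation of missing hypotension durations. Section IX.C describes the models for that purpose as "multivariate models of duration of IOH as a function of baseline and preoperative characteristics". Section IX.B likewise identifies potential covariates from baseline variables. Section VI classes multivariate analyses as supportive and outside the control of alpha.

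**The concern.** The outcome is minutes of MAP below 65 mmHg during surgery (section V.A), so it is complete when the operation ends. A covariate in a model meant to isolate the device effect should not be a consequence of the device or of the outcome. Sepsis recorded as an adverse event generally comes later and may be a result of hypotension. Blood loss accumulates while the device is guiding management and may be changed by it. Conditioning on such variables can remove part of the device effect, exaggerate it, or create an association that is not there.

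This matters because the design is single-arm with historical controls, and the primary test standardises for site only. The IX.D mixed model is the only planned analysis of the outcome that adjusts for patient case mix. A reader who doubts the comparability of the two groups will look to it first.

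**Working it through.** **1. Timing of the listed factors against the outcome**

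| Factor | When it is determined | Can the device or the outcome affect it? |
|---|---|---|
| Demographics, history, drugs, ASA class, baseline MAP | Before surgery | No |
| Surgical time | During surgery | Possibly, but it is also time at risk |
| Intra-operative blood loss | During surgery | Possibly, through device-guided care |
| Sepsis as an AE | Generally after the outcome | Possibly, by both |

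**2. The plan's own figures.** The SAP gives no figure for this model. From section V.A.1, the control mean is 28.2 min, its SD 42.5, the control N 19,446, and the expected reduction 25%, so the planned effect is 0.25 × 28.2 = 7.05 min. The sample size of 389 is reproduced with SD 42.5 in both groups:

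n = 42.5² / [7.05²/(1.960 + 1.282)² − 42.5²/19,446] = 389.5.

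No covariate enters this calculation, so changing the covariates leaves it as it is. (Which SD the plan meant to use is a separate matter.)

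**3. Would the variables survive elimination?** A factor's main effect is estimated on all 389 + 19,446 = 19,835 records. With residual SD 42.5:

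- Continuous factor, per SD: SE = 42.5/√19,835 = 0.30 min. A slope of only 1 min per SD gives z of about 3.3.
- Binary factor with prevalence p: SE = 42.5/√(19,835·p(1−p)). This is 0.60 min at p = 50%, 1.0 at 10% and 1.4 at 5%.

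Blood loss would therefore tend to be kept even if weakly associated. Suppose, as an assumption, that sepsis has 5% prevalence and a log-odds of 0.5 per SD of hypotension minutes. Septic and non-septic patients would then differ by about 0.5 × 42.5 = 21 min, roughly 15 standard errors, and sepsis would be kept too.

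**4. Effect of keeping blood loss.** Let the device shift blood loss by a SD and let hypotension rise b minutes per SD of blood loss, with a true total effect of -7.05 min. The blood-loss-adjusted effect is −7.05 − a·b. The values of a and b are assumptions. With b = 10:

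| a | Adjusted effect (min) |
|---|---|
| 0 | −7.05 |
| −0.1 | −6.05 |
| −0.2 | −5.05 |
| −0.3 | −4.05 |
| +0.2 | −9.05 |

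With b = 1 the same shifts move the estimate by only 0.1 to 0.3 min.

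**5. Effect of keeping sepsis.** This was simulated with 389 treated and 19,446 control patients, 300 repetitions, and sepsis near 5%:

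| Assumption on sepsis | Unadjusted | Sepsis-adjusted |
|---|---|---|
| Unrelated to hypotension | −6.98 | −6.98 |
| Log-odds 0.5 per SD of hypotension | −7.09 | −7.00 |
| Log-odds 1.0 per SD | −7.13 | −6.72 |
| 0.5 per SD, treated log-odds lower by 1 | −7.18 | −6.47 |
| 0.5 per SD, treated log-odds higher by 1 | −6.85 | −8.30 |

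The shift is about 0.1 to 0.4 min towards zero when sepsis depends on hypotension alone. It is about 0.7 to 1.5 min, in either direction, when the frequency or recording of sepsis also differs between trial and registry.

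**6. The imputation model.** Section IX.C builds it from baseline and preoperative characteristics. Section IX.D builds it from the model just described, whose candidates include intraoperative and adverse-event variables. The two descriptions give different covariates for the same imputation.

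**The case against.** The strongest reply is that nothing decisive rests on this model. Success is judged by the site-weighted t-test alone, and section VI classes multivariate work as supportive. The listed variables are candidates that must pass screening, review and elimination. That stands, and it limits the weight of the point. It does not answer it, because the review step has no stated criterion and the number of records favours retention.

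Blood loss may also mark the extent of surgery, so adjusting for it could remove some case-mix difference. That is fair, but the model cannot separate that role from a change caused by device-guided care. Surgical time is different again: it is partly time at risk for accumulating hypotensive minutes, and there is a real case for including it.

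Several stronger readings are tempting but not supported:

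- A reader might infer that elimination could remove the treatment term. The SAP names treatment separately from the factor of interest, so this is a strained reading. The text is merely silent on protecting treatment and site.
- A reader might infer that with 389 treated subjects real confounders would be dropped. Main effects are estimated on 19,835 records, so a 2-minute factor at 50% prevalence has z of about 2/0.60 = 3.3. Only rarer or weaker factors are at risk.
- A reader might infer that the SAP contradicts itself on the device-effect model. The section IX.C wording concerns imputation, and the conflict is confined to that use.
- Backward elimination in a supportive analysis, and post-baseline predictors in an imputation model, are matters on which statisticians differ. Neither is an error in itself.

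**Conclusion.** The point holds as a defect of the sensitivity analysis. Sepsis as an AE and intra-operative blood loss do not belong in a model of the device effect on intraoperative hypotension. If retained, they can bias that effect in either direction. Sections IX.C and IX.D also disagree on what enters the imputation model.

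The size cannot be derived from the SAP. Under the assumed associations shown, blood loss moves a 7.05-minute effect by 1 to 3 minutes and sepsis by about 0.1 to 1.5 minutes. Both shifts vanish if the device does not change blood loss, and if sepsis is unrelated to hypotension.

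A reader might infer that the adjusted estimate is certain to be biased, or that the trial has no valid check on confounding. The SAP supports neither. Bias requires that the device, the outcome or differential recording affects the variable, most listed factors are preoperative, and section IX.B adds a baseline comparability analysis. The primary test and the sample size are unaffected.

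**What to change.** In section IX.D:

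- Remove sepsis as an AE and intra-operative blood loss from the adjusted device-effect model, and use the preoperative factors already listed.
- State that treatment and site stay in the model whatever their P values.
- Report the adjusted treatment difference with its 95% CI, once with and once without surgical time, labelling the two models.

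In sections IX.C and IX.D, give one agreed list of covariates for the imputation model. If post-baseline predictors are wanted there, say so in both places.

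The cost is a change of SAP wording, slightly more analysis work, and possibly a less precise adjusted estimate. The listed preoperative factors are already planned, so they call for no new data.
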